### Assessment and measures

3.9

#### Neuropsychological evaluation

3.9.1

All participants will be evaluated by neuropsychological tests at 4 different moments: before the first cycle, with an intellectual screening and additional behavioral analysis; after the first cycle and before and after the second cycle. The tests will be applied by neuropsychologists with experience in the evaluation process and using the following instruments:

Characteristics of the sample:

Intellectual screening – Wechsler abbreviated intelligence scale^[42,43]^: for obtaining the estimated intelligence quotient 2 subtests will be used: the vocabulary subtest that evaluates semantic knowledge and the matrix ratio subtest that evaluates nonverbal logical reasoning ability, a task that evaluate fluid intelligence.Child behavior checklist^[44,45]^: this is a questionnaire that assesses social competence and behavioral problems in individuals aged 4 to 18, based on information provided by those responsible.Neuropsychological tests to measure results:TAVIS-4^[46]^: assesses children aged 6 to 17. The child presses and holds a button on a joystick when it sees a target on a screen. There are 2 versions: ages 7 to 11 (target stimulus – 6 minutes) and ages 12 to 17 (10 minutes). Each task scores: reaction time, commission errors, omission errors, and number of hits. “Commission Errors” records an answer when it should not be given; Error by omission is the lack of response to a target stimulus; Average reaction time (in milliseconds) is the time the child takes to push the button from when the stimulus appears on the screen. Task 1 (selective attention) involves pressing a button when the target stimulus appears. Task 2 (alternating attention) alternates between 2 types of answers to identify identical geometric shapes of the same color. Task 3 assesses sustained attention (concentration) through a continuous performance test.Digit span subtest of the WISC-IV^[42]^: is an attention and working memory measure applied to forward (auditory attention) and backward (working memory) digit movement. The examiner reads aloud a sequence of numbers. The child repeats the numbers in the same order in which they were spoken (forward) and then repeats the numbers in reverse order (backward).Corsi block^[47]^: evaluate visual working memory. Subject repeats sequences of touches in different cubes. In the forward order, visual attention is tested and in backward order visuospatial sketch of working memory is tested.Inhibition is a subtest of attention and executive functions from the developmental neuropsychological assessment battery second edition (NEPSY II)^[48,49]^: assesses ability to inhibit desire to engage in a pleasant task and/or either stop an automatic behavior or alternate between stop and automatic behavior. The examinee looks at a series of stimuli shapes/arrows and must name the shape or direction or give an alternative response, depending on the stimulus color. Errors occur when an incorrect answer is given or is skipped or not corrected. Anything unanswered due to lack of time is considered an incorrected error. Self-corrected errors occur when an incorrect answer is then corrected. Total of errors is the sum of uncorrected errors and self-corrected errors for each condition (naming: select information; inhibition: ability to inhibit an automatic response; switching: ability to switch attention).At the end of the research the results will be disclosed to those responsible via a report written by the relevant researcher.

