In the past decades, several interventions and diagnostic tools have been tested for brain and mind disorders.^[11–23]^ Among them, tDCS is an emerging neuromodulation technique that uses low-intensity electrical stimulation to modulate target brain regions and has a potential therapeutic benefit because the neurophysiological effect of current applied is durable over time after the stimulation ceases.^[24]^ The anodic tDCS is based on an electric current from a generator that aims to stimulate certain cortical areas, causing an increase in local cerebral blood flow.^[25]^ This tool has been currently used in the treatment of various psychiatric and neurological disorders such as schizophrenia,^[26]^ dyslexia,^[27]^ autism,^[28]^ cerebellar ataxia,^[29]^ epilepsy,^[30]^ unipolar and bipolar depression,^[31]^ since it is considered safe and relatively less expensive than other noninvasive brain stimulation approaches.^[32,33]^ Advantages of the cost-effectiveness of tDCS could be even more important considering low-middle income countries.^[34,35]^

Previous studies have shown that tDCS is both a safe and an encouraging option in the treatment of ADHD,^[10,36–40]^ proving the validity of researching this method and its adverse effects. In addition, some children and adolescents present contraindications for the use of psychoactive drugs, necessitating the use of alternative methods. The pilot open-label trial conducted by Bandeira et al^[38]^ showed improvement in some executive functions such as selective attention and inhibitory control using tDCS in children and adolescents with ADHD. However, further studies with appropriate randomization, blinding, and larger sample sizes should be performed to further investigate these findings. The main objective of this study is to widen the scope of the previous investigation and to prove reproducibility of the findings as well as ensure safety of the technique in this population.

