### Sample calculation

3.4

The sample size calculation was performed based on a pilot study. We used the variable “errors by default” of visual attention test (TAVIS) test as the primary outcome. Considering the level of significance of 5%, the power of 80%, the mean difference between paired groups of 1.2 and the standard deviation of 1.24, the sample size calculation resulted in 11 subjects. Assuming 25% of dropout, our final sample size was 14 subjects.

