### Blinding

3.6

The tDCS devices will be covered during the procedure and no patient or relative will have contact with them. To certify blinding of participants in the sham group in relation to the sensation of current flow involved in the procedure, the device will be switched on for 1 minute at the beginning of the stimulation, turned off for the subsequent 28 minutes and reconnected at the last minute of stimulation. The family, the research subject, the evaluators, and the statistician will be blind to the group to which the subject belongs (“Sham” or “Active”). At the end of the 5 tDCS or sham-tDCS sessions in the first stage of the study, patients and their families will be asked if they believed they were in the intervention or control group. After the 30 day washout period, the second stage of the study will be carried out in the same manner, with the same questioning at the end of the 5 sessions of tDCS or sham-tDCS.

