
### Statistical analyses

3.10

To test the hypotheses of the study various inferential statistical tests will be performed with a comparison of means and medians (Student *t* test and Wilcoxon) using the SPSS statistical package for Windows. In the inferences, a significant result will be considered if the probability of type I error is ≤0.05 (5%).

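### Section 3.10 does not say which score is compared and leaves the pre-test before each period unadjusted; a baseline-adjusted crossover contrast should be primary

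*Protocol article*

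**What the plan says.** Section 3.9.1 (Neuropsychological evaluation) sets four test occasions: "before the first cycle, with an intellectual screening and additional behavioral analysis; after the first cycle and before and after the second cycle". Each of the two periods therefore has a pre-test and a post-test.

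Section 3.10 (Statistical analyses) says that "various inferential statistical tests will be performed with a comparison of means and medians", names Student's t test and the Wilcoxon test, and sets a 5% significance level. It does not define the score that enters these tests, and it mentions no covariate or period term.

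Section 3.4 (Sample calculation) sizes the trial on a paired comparison, using "the mean difference between paired groups of 1.2 and the standard deviation of 1.24". It does not say whether this is a difference in post-scores or in changes.

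On persistence, the Introduction says that "the neurophysiological effect of current applied is durable over time after the stimulation ceases". Section 3.6 (Blinding) describes the crossing: "After the 30 day washout period, the second stage of the study will be carried out in the same manner". Section 3.8 (Interventions) puts 8 children in the active-first sequence and 7 in the sham-first sequence. No section says what the second pre-test is for.

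**The concern.** Two analyses fit the wording of section 3.10, and each has a weakness that the data already planned could reduce.

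- **Post-scores.** These leave both pre-tests unused. If some of the active effect is still present after the washout, the sham period of the active-first children is contaminated, and the contrast shrinks with nothing in the analysis to show it.
- **Within-period changes.** These use the pre-tests and cancel any carry-over that is stable through period 2. They also add the noise of two further measurements, which costs precision unless the active-minus-sham differences at pre-test and post-test are well correlated.

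Adjusting for the pre-test difference as a covariate is never less precise than either in large samples, but a plain t or Wilcoxon test cannot do it. With 15 children, avoidable variance matters. The choice between the two readings should also be fixed before results are seen.

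**Working it through.** **1. The plan's own figure.** Inputs from section 3.4: difference 1.2, SD 1.24, significance level 5%, power 80%. For a two-sided paired t test the noncentrality is (1.2/1.24)·√n. Power is 0.777 at n = 10 and 0.824 at n = 11, so the stated 11 is reproduced; 11 × 1.25 = 13.75 gives the stated 14. At the 15 children of section 3.8, power is 0.936.

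**2. Variance of the three contrasts.** Assume equal variance at all four occasions (set to 1), correlation rw between pre-test and post-test of the same period, and rb between any two scores from different periods. The documents give neither; rw 0.6 to 0.8 and rb 0.5 to 0.6 are assumed.

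- Post-scores: 2(1 − rb)
- Change scores: 4(1 − rw)
- Adjusted: 2(1 − rb)(1 − r²), where r = (rw − rb)/(1 − rb) is the correlation between the pre-test difference and the post-test difference

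| rw, rb | r | Post | Change | Adjusted | Adjusted vs post | Adjusted vs change |
|---|---|---|---|---|---|---|
| 0.6, 0.6 | 0 | 0.80 | 1.60 | 0.80 | 0% | −50% |
| 0.6, 0.5 | 0.2 | 1.00 | 1.60 | 0.96 | −4% | −40% |
| 0.8, 0.6 | 0.5 | 0.80 | 0.80 | 0.60 | −25% | −25% |
| 0.8, 0.5 | 0.6 | 1.00 | 0.80 | 0.64 | −36% | −20% |

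Change scores have the larger variance than post-scores when r < 0.5, equal variance at r = 0.5, and smaller variance above it.

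**3. In power, at the plan's 11 evaluable children.** Take 1.24 as the SD of the post-score difference. The adjusted analysis has SD 1.24·√(1 − r²) and n − 3 degrees of freedom (period term and covariate). The paired t test on changes has SD 1.24·√(2 − 2r). The plain paired t test on post-scores has power 0.824.

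| r | Adjusted: power (n for 80%) | Change: power (n for 80%) |
|---|---|---|
| 0 | 0.80 (11) | 0.54 (19) |
| 0.3 | 0.84 (11) | 0.69 (14) |
| 0.5 | 0.90 (10) | 0.82 (11) |
| 0.7 | 0.97 (8) | 0.96 (8) |

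**4. Carry-over in a post-score contrast.** Let a fraction c of the effect remain throughout period 2 in the 8 active-first children. The expected paired contrast is 1.2 × (1 − 8c/15). Power is by simulation of the paired t test.

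| c | Expected contrast (8:7) | Power, 15 children (8:7) | Power, 11 children (6:5) |
|---|---|---|---|
| 0 | 1.20 | 0.94 | 0.82 |
| 0.25 | 1.04 | 0.85 | 0.70 |
| 0.5 | 0.88 | 0.70 | 0.54 |
| 1 | 0.56 | 0.29 | 0.20 |

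**5. What the covariate does to carry-over.** With a period term the two sequences count equally, so stable carry-over takes c/2 of the effect from a post-score contrast: at c = 0.5, 1.2 × (1 − 0.25) = 0.90. The covariate removes the fraction r of that bias. At r = 0.2 the contrast is 1.2 × (1 − 0.25 × 0.8) = 0.96; at r = 0.5 it is 1.2 × (1 − 0.25 × 0.5) = 1.05. Change scores give 1.20.

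**6. What the second pre-test can show.** Compare the sequences on the change from first to second pre-test, with SD 1.24 assumed for that change. With 15 children, power is 0.14 at c = 0.5 and 0.41 at c = 1.

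**The case against.** The strongest reply is that section 3.10 is brief and does not fix post-scores. A paired test on within-period change fits its wording, uses the second pre-test and cancels stable carry-over. Model details may sit in a statistical analysis plan that is not shown. This stands in part. A reader might infer that the protocol never uses the second pre-test, or that the tDCS effect will be underestimated. The documents support neither: the dilution figures hold only if post-scores are compared, and if carry-over fades during period 2, change scores would overstate the effect. What remains is that the article names its tests, that neither can adjust for a pre-test, and that the analysed score is undefined.

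A reader might also infer that the Introduction contradicts the washout. It does not. The durability described there is neurophysiological and has no stated duration, so it does not show that test scores stay altered beyond 30 days.

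Nor is the precision gain certain. At r = 0 adjustment gains nothing over post-scores and loses about two points of power (0.80 against 0.824 with 11 children). Finally, adjustment does not cure carry-over: at r of 0.2 to 0.5, 50% to 80% of a stable carry-over bias stays, and change scores do better on that count. This is why both analyses are needed, with one named as primary.

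**Conclusion.** The point holds as a matter of analysis choice. Section 3.10 leaves the compared score open and plans only unadjusted tests, although a pre-test is collected before each period. Over the assumed correlations, covariate adjustment lowers the variance by 0% to 36% against post-scores and by 20% to 50% against change scores. The worst case is a loss of about two power points, which makes it the safer choice while the correlations are unknown.

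Carry-over is a possible risk, not something the documents show. Its size, 1.2 falling to 0.88 with half the effect persisting, applies to the post-score reading alone. The results rest on equal variances, on the assumed correlations and persistence fractions, and on reading 1.24 as the SD of the post-score difference.

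**What to change.** In section 3.10:

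1. State the primary contrast as the active-minus-sham difference in post-scores, from a crossover model with a period term and each child's difference between the two period pre-tests as covariate. This replaces the unadjusted t and Wilcoxon tests as the primary analysis.
2. Name the change-score analysis as a sensitivity analysis, because the covariate removes only part of any stable carry-over.
3. Report the between-sequence difference at the second pre-test with its confidence interval, as a description only. Its power is too low to decide which analysis is used.

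No visit or measurement is added; all four assessments are already planned. The covariate costs one degree of freedom and the period term another. If the pre-test and post-test differences are nearly uncorrelated, the effect on power is negligible or slightly negative. The change is more than a clarification, since a model takes the place of the named tests as primary.

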### Secondary

2.2

To identify the adverse effects related to tDCS in children and adolescents with ADHD.

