### Interventions

3.8

After selecting the sample according to the aforementioned criteria and neuropediatric evaluation, children diagnosed with ADHD will participate in a neuropsychological assessment in which the intellectual level estimation and its performance in the processes of attention, operational memory, and inhibitory control will be investigated. The Swanson, Nolan, and Pelham – IV questionnaire assessing the diagnostic criteria for ADHD from the DSM-5 will be applied to the parents.

A total of 15 individuals will be selected, randomly assigned in 2 groups, 8 of whom were initially in the tDCS group and 7 in the sham group. It will be made clear to those responsible and to the relevant child that tDCS may not be applied. During the stimulation, the same conditions will be reproduced in both groups, except for active treatment in the sham group. The patient will be informed about the procedure before the beginning of the study, with the device being used for a first perception of the current flow for a few seconds.

The tDCS consists of an application of a direct electric current of low amplitude (2 mA) for 30 minutes from 2 electrodes (5 cm × 7 cm) embedded in saline solution. The anode will be positioned in the left anterior dorsal prefrontal cortex (F3 according to the electroencephalogram system 10–20) and the cathode in the supraorbital region on the opposite side. The device used will be the Striat (Ibramed, Amparo-SP, Brazil), approved by the Brazilian National Health Agency (ANVISA). During the stimulation period participants will participate in playful activities involving memory and attention, such as the “Super Lynx” and “Genius” games. They will be carried out by an appropriately trained individual, in 5 sessions, 1 per day, and in the presence of a physician trained to deal with possible intercurrences. Participants may withdraw from participating in the study at any time according to the informed consent form.

After 1 month, the groups will be crossed. Thus the 8 children initially stimulated will be part of the sham group in the second phase and the children initially in the sham group will then receive active stimulation. Before and after the new cycle of stimulation, neuropsychological evaluations will be carried out by applying the aforementioned tests. The family, the research subject, the evaluators, and the statistician will be blind to the subject's group.

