At the end of each session, participants and their families will be asked about the presence of the most prevalent adverse effects related to tDCS reported in previous studies.^[36,38,41]^ Any adverse event identified as severe by the attending physicians will be a criteria for exclusion from the study.

The participants will be contacted by telephone the day before the intervention to confirm their participation, thus avoiding possible absences. In order to promote participant retention and complete follow-up, it will be collected outcome data from participants who discontinue or deviate from intervention protocols. In addition, to promote data quality, the data values will be checked by 2 external individuals to avoid incorrect analysis.

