Following randomized, double-blind, sham-controlled studies were performed with adolescent dorsolateral prefrontal cortex stimulation, one of which showed improvement of executive function with anodic stimulation and improvement of inhibitory control with cathodic stimulation.^[51]^ Other study showed that anodic stimulation caused a significant reduction of the clinical symptoms of inattention and impulsivity in patients with ADHD compared to the sham-group.^[36]^ Moreover, in a different study anodal stimulation improved motor performance, but worsened accuracy in the working memory paradigm.^[42]^

We hope, with our randomized, cross-over, triple-blind, sham-controlled protocol, to find statistically significant results regarding patterns of attention and inhibitory control identified by the neuropsychological test battery performed.

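### No adverse-effect enquiry is stated after the fifth session of either cycle, and the 7 children given active stimulation last have no stated safety contact beyond the post-cycle test

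*Protocol article*

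**What the plan says.** Section 2.2 gives the secondary aim: "To identify the adverse effects related to tDCS in children and adolescents with ADHD". The Introduction goes further and sets out to "ensure safety of the technique in this population".

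Adverse effects are collected under section 3.8: "At the end of each session, participants and their families will be asked about the presence of the most prevalent adverse effects related to tDCS". Each cycle has five sessions, one a day. The article states no other adverse-effect enquiry.

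Section 3.9.1 lists four neuropsychological assessments: one before the first cycle, then "after the first cycle and before and after the second cycle". It gives no time window for the test that follows a cycle.

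On sequence, section 3.8 puts 8 children on active stimulation first and 7 on sham first. At the crossover "the children initially in the sham group will then receive active stimulation". Section 3.6 gives the gap: "After the 30 day washout period, the second stage of the study will be carried out in the same manner". The Introduction says of stimulation that "the neurophysiological effect of current applied is durable over time after the stimulation ceases", without giving a duration.

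**The concern.** The plan takes it that stimulation can act beyond the sessions: it calls the effect durable and leaves 30 days for it to fade before the second cycle. It does not carry that reasoning over to harms. The stated enquiry stops when the fifth session of a cycle ends, so an effect that starts later, or starts in a session and persists, has no planned place to be recorded.

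There are two consequences. In the active-first children, a late effect of active stimulation may first be reported at a sham session in cycle 2 and be counted under sham, which would blur the comparison of the two conditions. In the sham-first children, a late effect has no stated route into the data once the post-cycle test is over. The participants are minors and identifying adverse effects is the only secondary aim, so the gap bears on a stated purpose of the trial.

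**Working it through.** **Inputs.** 15 children, 8 active first and 7 sham first (section 3.8). Five sessions per cycle, with an enquiry as each one ends (section 3.8). Four test occasions, the last after cycle 2 (section 3.9.1). Washout of 30 days (section 3.6).

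**The plan's own calculation.** The only calculated figure is the sample size in section 3.4. With effect size 1.2/1.24 = 0.968 and a paired t test at two-sided 5% (sidedness is not stated, so this is assumed), power is 77.7% at n = 10 and 82.4% at n = 11, so 11 is reproduced. The final 14 matches 11 × 1.25 = 13.75, rounded up. None of this depends on safety collection, so the present point leaves it untouched.

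**What is stated after active stimulation, by sequence.**

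| | Active first (8) | Sham first (7) |
|---|---|---|
| Enquiries at active sessions | 5 | 5 |
| Test after the active cycle | yes | yes |
| Adverse-effect enquiry stated at that test | no | no |
| Enquiry stated during the following 30 days | no | none stated |
| Return after about 30 days | cycle 2 pre-test (no enquiry stated), then 5 sham sessions (enquiry at each) | none stated |

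The enquiry schedule itself is the same in both columns: 5 per cycle, 10 per child. What differs is the last row, and that return is a by-product of the crossover rather than a planned safety visit.

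**Share of active exposures affected.** 15 − 8 = 7 children receive active stimulation last. 7/15 = 46.7% have no stated return, and 8/15 = 53.3% have one.

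**What that means for late effects (illustration).** Treat a child as informative about a late event only if the child is contacted again after about a month.

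- With zero late events in n children, the one-sided 95% upper bound is 1 − 0.05^(1/n). For n = 8 this is 31.2%; for n = 15 it is 18.1%.
- The chance of seeing at least one event at true rate p is 1 − (1 − p)^n. The documents give no late-event rate, so a range is assumed:

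| Assumed rate | 8 children | 15 children |
|---|---|---|
| 5% | 34% | 54% |
| 10% | 57% | 79% |
| 20% | 83% | 96% |

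The column for 8 is generous to the current plan. It supposes that a late event comes out at the return visits and is credited to active stimulation, although no enquiry is stated before the first sham session has ended. Neither column allows for dropout.

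**The case against.** The strongest reply is that section 3.8 treats everyone alike: five enquiries per cycle, under active and sham, in both sequences. That is correct. A reader might infer from the crossover that adverse effects are collected over windows that differ by randomised sequence, or that the active-first children get 30 days of safety observation and the others none. The article does not support this. No enquiry is stated in the washout or at the cycle 2 pre-test, so planned collection stops at the fifth session for all 15. Only the opportunity for a late effect to come to light differs.

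Two other strong readings also fail. One is that the sham-first children leave the trial straight after their last active session. They have a post-cycle test with no stated window, and sections 3.9.1 and 3.11 promise families results and a report. Those are later contacts, though for disclosure and not for collecting safety data. The other is that the Discussion documents a harm that outlasts stimulation. It says that in another study anodal stimulation improved motor performance "but worsened accuracy in the working memory paradigm", with nothing on how long that lasted. Nor does calling the neurophysiological effect durable show that any harm is.

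It can also be said that a condensed article may leave a late safety contact to the full protocol, and that asking after every session already serves the secondary aim. The first is possible and limits how firmly the absence can be asserted. The second holds for effects felt during or right after a session, but not for those that appear or persist later. The article spells out both the enquiry rule and a counted list of assessments, so it is fair to comment on what those two leave uncovered.

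**Conclusion.** The point holds in a limited form. As stated, no adverse-effect enquiry follows the fifth session of either cycle for any of the 15 children. For the 7 sham-first children, 47% of active exposures, there is also no stated safety contact beyond the post-cycle test. For the 8 active-first children a late effect could surface in cycle 2, but might be attributed to sham. This fits poorly with the trial's safety aim, its 30-day washout and its description of the effect as durable.

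The conclusion rests on three assumptions: that the article states the enquiry schedule in full, that the cycle 2 pre-test falls at about the end of the washout, and that late or persisting effects are possible. The documents neither quantify nor exclude such effects. The probabilities above illustrate the size of the gap and do not predict harm. Efficacy, alpha, power and sample size are unaffected. The plan should be amended, but the gap does not undermine the trial.

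**What to change.** In section 3.8, extend the adverse-effect enquiry. Put the same questions, plus one open question on new or persisting problems, to every family:

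- at the test after each cycle;
- at the cycle 2 pre-test, before the first cycle 2 session, about 30 days after cycle 1;
- in one telephone call about 30 days after the last cycle 2 session.

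Report adverse effects after active and after sham over the same window, from the first session of the cycle to about day 30. Attribute events reported at the cycle 2 pre-test to the condition received in cycle 1.

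This adds 4 enquiries per child. Three use visits already planned; the fourth is a new call, so 15 × 1 = 15 calls in all. The team already telephones families before the intervention. The downside is that the last child finishes about 30 days later. The change concerns data collection only and leaves treatment as it is. If the full protocol already contains such a contact, it is enough to state it.
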